# Effects of rTMS over the contralateral M1 combined with NMES on pain and functional mobility in primary frozen shoulder: study protocol for a 4-week double-blind, randomized, sham-controlled trial

**DOI:** 10.3389/fneur.2025.1722035

**Published:** 2026-02-16

**Keywords:** frozen shoulder, function, neuroplasticity, NMES, pain, rTMS

## Abstract

**Background:**

Repetitive transcranial magnetic stimulation (rTMS) with low and high frequency as well as neuromuscular electrical stimulation (NMES) have been proved efficacy, respectively, on pain and dysfunction of frozen shoulder (FS). Evidence suggests that the integration of central neuromodulation and peripheral stimulation techniques, establishing a closed-loop neural circuitry, yields superior therapeutic outcomes compared to isolated rehabilitation modalities. Therefore, the purpose of this study is to evaluate the clinical effectiveness and neuro-biomechanism of combining rTMS and NMES in alleviating pain and motor deficit of primary FS patients.

**Methods:**

This will be an assessor and patients blinded, sham controlled and randomized controlled clinical trial involving a 4-week intervention and a 6-month follow-up. 117 people with FS will be equally allocated to the sham-rTMS + NMES group (Group A), low frequency (LF)-rTMS + NMES group (Group B) and high frequency (HF)-rTMS+ NMES group (Group C) through stratified randomization. Interventions will be provided in 5 sessions per week, with a total of 20 sessions. The primary outcome measurements will be the score of Constant-Murley. The secondary outcome measurements will include polysomnography, quality of life (QOL) by SF-36, muscle biomechanics by surface electromyography (sEMG), motor evoked potential (MEP), brain neuroplasticity by magnetic resonance imaging (MRI). Evaluations will be performed at six time points, including at baseline, 2 weeks and 4 weeks from the start of treatment, and 1 month, 3 months and 6 months following the end of treatment. Two-way analysis of variance with repeated measures will be applied to examine the main effects of the group, the time and group-time interaction effects for all outcomes.

**Discussion:**

The study will be the first protocol to demonstrate the effectiveness of rTMS with/without NMES for improving shoulder function and pain management after FS and compare the efficacy of LF-rTMS and HF-rTMS. The results of the study may guide the design of more effective treatment methods for FS rehabilitation.

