Aim 1: To evaluate the efficacy of NMES combined with rTMS over the contralateral M1 area in reducing pain intensity and improving functional ability in patients with FS. And to compare the efficacy of LF-rTMS+NMES and HF-rTMS+NMES in patients with FS.

Aim 2: To investigate the correlation between the clinical efficacy and neuro-biomechanism of cortical alternation in patients with FS after conducting systematic evaluations both before and after treatment.

Aim 3: Based on this study protocol and its anticipated outcomes, clinicians can develop innovative management strategies for pain and motor function in patients with FS, aiming to achieve effective therapeutic results.

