## Methods and analysis

### Study design

This will be an assessor and patients blinded, sham-controlled, randomized controlled clinical trial (RCT) involving a 4-week intervention and 6-month follow-up. A total of 117 patients with FS will be recruited and randomly assigned to the sham rTMS +NMES group (Group A), LF-rTMS+NMES group (Group B) and HF-rTMS+NMES group (Group C) at a ratio of 1:1:1. Figure 1 depicts a concise flowchart of the entire study, and Table 1 provides the schedule of events. The study protocol (2025-7th-HIRB-042) was approved by the Ethics Committee of the Seventh People’s Hospital of Shanghai University of Traditional Chinese Medicine and registered in the Chinese Clinical Trial Registry (ChiCTR2500098406).

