### Selection of subjects

#### Inclusion criteria

Patients aged ≥18 years old with unilateral shoulder pain.A minimun 25% reduction in the ROM in at least two planes compared to the unaffected shoulder (34).Patients with a duration of pain ≤ 9 months and a visual analogue scale (VAS) for shoulder pain ≥ 3.Normal shoulder X-rays.

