### Intervention methods

The intervention will be administered at the rehabilitation medical center of the Seventh People’s Hospital of Shanghai University of Traditional Chinese Medicine. All participants will receive the conventional rehabilitation program (CRP) recommended by the FS rehabilitation guidelines (37), which will include low-high grade joint mobilization, stretching exercise, passive and active limb movements, muscle strengthening, and self ROM exercises like different directions reaching, grasping and daily actions that are motivational and appropriate for the participants. Based on the CRP (30 min), control group C will receive Sham rTMS (20 min) + NMES (20 min); Intervention group A will receive LF-rTMS (20 min) + NMES (20 min); and Intervention group B will receive HF-rTMS (20 min) + NMES (20 min). The intervention for the three groups will be provided for 20 sessions (5 sessions per week, 4 weeks), each lasting 70 min.

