### Clinical effectiveness

#### Primary outcome measures

The CMS is a typical shoulder function metric. Effective CMS implementation has shown its validity, reliability, and responsiveness in shoulder pathology identification (45). The minimal clinically important difference (MCID) considered for the score is 17 points (46). The CMS scale evaluates four dimensions associated with shoulder pathology: two subjective factors—pain and activities of daily living (ADL)—and two objective factors—ROM and strength. The CMS employs the presence or absence of “unaffected sleep” as a criterion for scoring shoulder function (47). The subjective components can receive up to 35 points and the objective 65, culminating in a total possible score of 100 points, with higher values indicating superior functionality (48).

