In summary, the study protocol will demonstrate the effectiveness of rTMS with/without NMES for improving shoulder function and pain management after FS and compare the efficacy of LF-rTMS and HF-rTMS. The rTMS combined with NMES may have a potential opportunity to better improve the shoulder function of FS patients. These results of the study will provide high-quality evidence to guide the design of more effective treatment methods for FS rehabilitation.

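### The stated rTMS with/without NMES comparison has no matching arm, and Aim 1's pain objective is tied to no named pain outcome

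*Protocol article*

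**What the plan says.** **The claim about NMES.** The Discussion part of the abstract says the study will "demonstrate the effectiveness of rTMS with/without NMES for improving shoulder function and pain management after FS". The last paragraph of the article's Discussion says the same: "the study protocol will demonstrate the effectiveness of rTMS with/without NMES for improving shoulder function and pain management after FS".

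**The arms.** Study design allocates patients to the "sham rTMS +NMES group (Group A), LF-rTMS+NMES group (Group B) and HF-rTMS+NMES group (Group C) at a ratio of 1:1:1". Intervention methods puts the conventional rehabilitation program under every arm and gives 20 minutes of NMES to each, including the sham arm.

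**The pain objective.** Aim 1 is to evaluate NMES combined with rTMS "in reducing pain intensity and improving functional ability in patients with FS", and to compare LF with HF.

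**Where pain is measured.** Entry requires "a visual analogue scale (VAS) for shoulder pain ≥ 3", and randomization is stratified by VAS band (3–4, 5–6, 7–10). VAS is not in the assessments of Table 1 and is not described under Outcomes. The primary outcome is the CMS, with four dimensions: pain, ADL, ROM and strength. Its scoring is given as follows: "The subjective components can receive up to 35 points and the objective 65". The SF-36 section lists pain as one of its domains. Table 1 schedules CMS and SF-36 at baseline, 2 weeks, 4 weeks, and 1, 3 and 6 months after treatment. The Outcomes section sets the primary endpoint at four weeks.

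**The concern.** The article makes two statements about what the trial will show that its own arms and outcome list do not back.

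First, a claim about rTMS with and without NMES needs patients who get rTMS and no NMES. If none exist, a report that keeps the phrase would credit the trial with a comparison that was never randomized. The background makes the point matter more, because it argues that central and peripheral stimulation together outperform either one alone.

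Second, pain is in the title, the stated purpose and Aim 1. If no pain measure is named as an outcome, the pain conclusion has two possible sources. It may be read off a total score that mostly measures something else. Or it may rest on a sub-score chosen after the data are seen, which is the choice that naming an outcome in advance removes.

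**Working it through.** **1. The plan's own sample size.** Inputs from Sample size calculation: f = 0.25, k = 3 groups, m = 6 measurements, ρ = 0.5, α = 0.05, power 0.80. For the between-groups F test of a repeated-measures ANOVA:

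λ = f²·N·m / (1 + (m − 1)ρ), with df = k − 1 and N − k.

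At N = 93: λ = 0.0625 × 93 × 6 / (1 + 5 × 0.5) = 34.875 / 3.5 = 9.96, df 2 and 90, power 0.8001. At N = 90 the power is 0.786, so 93 is the minimum. With 20% drop-out, 93 / 0.80 = 116.25, rounded up to 117 = 3 × 39. Both stated figures reproduce. The calculation compares the three groups as randomized. It contains no NMES term, so rewording the claim leaves 93 and 117 unchanged.

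**2. Which contrasts exist.** Write μ(r, n) for the mean under rTMS type r, with n = 1 if NMES is given and n = 0 if not. Conventional rehabilitation is given throughout.

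- Observed: μ(sham, 1), μ(LF, 1), μ(HF, 1).
- Not observed: μ(sham, 0), μ(LF, 0), μ(HF, 0).

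The estimable differences are μ(LF, 1) − μ(sham, 1), μ(HF, 1) − μ(sham, 1) and μ(LF, 1) − μ(HF, 1). What NMES adds to rTMS is μ(LF, 1) − μ(LF, 0), and likewise for HF. The second term of each is observed in 0 of 3 arms. In a regression, the NMES indicator equals 1 for every patient and cannot be separated from the intercept. More patients do not change that. Synergy would need μ(sham, 0) as well.

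The arm letters do not affect this. Study design makes Group A the sham group, while Intervention methods says "control group C will receive Sham rTMS (20 min) + NMES (20 min". That is a separate inconsistency; NMES is in every arm under either labelling.

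**3. Where pain is captured.**

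- VAS pain: two uses, both at entry (eligibility and randomization stratum). Scheduled after entry: none.
- Stand-alone pain outcomes after baseline: 0.
- Instruments with a pain component after baseline: 2 (CMS and SF-36), each at 6 − 1 = 5 post-baseline visits.

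**4. What the CMS total says about pain.** Pain and ADL carry up to 35 points; ROM and strength carry up to 65; 35 + 65 = 100. So 65 / 100 = 65% of the total is neither pain nor ADL. The article's MCID is 17 points.

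- All 17 points could come from the 65 objective points with pain unchanged.
- They could also come from pain and ADL alone, which takes 17 / 35 = 48.6% of that range.

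A difference in the total is therefore compatible with a pain effect and with none. By itself it cannot settle the pain part of Aim 1.

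**The case against.** **The phrase about NMES is a slip, not a design fault.** It appears only in the abstract's discussion and the closing summary. The purpose in the Background and Aim 1 speak of combining rTMS with NMES and of LF versus HF, and a sham, LF and HF comparison on top of NMES tests those. No aim promises the separate value of NMES. This stands, and it limits the remedy to wording. It does not remove the contradiction, which occurs in two of the places readers look first. The design would support the reverse phrase, NMES with or without rTMS.

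**Pain has not been forgotten.** Sample size calculation treats pain and function as the primary outcome and presents the CMS as sensitive to both, so the authors chose the CMS as their pain-and-function measure. The sub-scores come with the instrument. Which of them is analysed separately is often left to a full protocol or SAP, and neither is shown. Most of this stands: a reader might infer that the trial cannot answer its pain question, and the documents do not support that, because the pain components of the CMS and SF-36 are scheduled at every visit. What remains is narrower. The article sets out its outcomes and assessment schedule in detail and states pain intensity as an aim, yet it links that aim to no pain measure.

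**Harm to the pain result is not shown.** A reader might infer that a true pain effect would be lost in the total, or that a ROM gain would be reported as pain relief. Neither is established. The article gives no maximum for pain apart from ADL, so dilution cannot be sized, and the joint ceiling of 35 is about twice the 17-point MCID. Data analysis contains no rule that would present a ROM gain as analgesia.

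**Conclusion.** The point holds in two limited parts, and both should be corrected.

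(a) The statement about rTMS with and without NMES contradicts the design: 0 of 3 arms omit NMES. Efficacy claims can reach only as far as LF- or HF-rTMS versus sham, each added to NMES and conventional rehabilitation, and LF versus HF. This rests only on the arm descriptions. It would be wrong to conclude that the design fails its aims; the add-on and frequency questions of Aim 1 are both testable, and the sample size is unaffected.

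(b) Aim 1's pain objective has no named pain-specific outcome. The CMS total cannot stand in for one, since 65 of its 100 points are ROM and strength and the other 35 are shared between pain and ADL. This is a gap in naming, not in data collection. It assumes that the outcome list and Table 1 are complete as published. If an unseen SAP already names a pain sub-score, the article only needs to agree with it.

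**What to change.** (a) In the abstract's discussion and the closing summary, replace the phrase with: *LF- or HF-rTMS versus sham rTMS, each added to NMES and conventional rehabilitation*. Confine efficacy claims to that contrast and to LF versus HF. This is a wording change only; 93 and 117 stay as they are.

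(b) Name the CMS pain sub-score as a secondary outcome at the four-week primary endpoint, analysed by the same between-group method as the CMS total. Rest pain claims on it and not on the total. The sub-score comes with an instrument already scheduled at all six time points, so nothing new is collected. The cost is one more secondary test to report. Make the change before outcome data are analysed.

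Optionally, repeat the entry VAS at remaining visits. That would need an amendment. Recruitment opened on 1 September 2025, so values for visits already completed could not be recovered.

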**Clinical trial registration:**

ChiCTR2500098406.

## Introduction

Frozen shoulder (FS), also known as adhesive capsulitis, is a persistent musculoskeletal disorder that manifests as severe insidious onset pain and functional constraint (1). Primary FS cause a progressive and excruciating loss of shoulder active and passive range of motion(ROM) without a known cause (2). FS affects 8% of men and 10% of women worldwide, with a lifetime frequency of 2 to 5% in the fifth and sixth decades. Instead of treating FS as self-limiting and proceeding through three overlapping stages without supervised intervention, evidence-based physiotherapy guidelines classify it as ‘pain predominant’ or ‘stiffness predominant’ (3). Between 7 and 50% of FS patients do not achieve normal ROM and endure symptoms for years with 6% lasting over 7 years (4, 5). Given that FS has proven resistant to treatment, exploration of emerging treatments is warranted (6).

The primary mechanism of shoulder pain in FS was seen as a peripheral nociception, characterized by elevated pro-inflammatory cytokines and neuroimmune system activation (7, 8). However, the pathophysiology of FS is intricate, with central pain pathways also playing a crucial role in patients with FS (9). FS patients exhibit more extensive pain regions, increased allodynia, hyperalgesia, catastrophizing, and central sensitization for pain in comparison to healthy individuals (10, 11). As the FS remains, the central nervous system may undergo potential neuroplastic changes that cause regional functional abnormalities (12), modifications in the pain modulation pathway (13) and network reorganizations (14, 15). These changes indicate a link between functional and morphological brain changes and neuroplasticity and neurobiological mechanisms generated by pain, representing cerebral cortex functional remodeling (16), similar to other chronic pain conditions (17, 18). Shoulder pain of FS is a continuous state, so FS patients both encompassing daytime pain and result in physical dysfunction and activity limitations and associated with risk of impaired sleep efficiency, length, and quality due to nocturnal shoulder pain and 34% of FS patients experience sleep disturbance and emotional disorders (19, 20, 21). The interplay of shoulder pain and sleep disturbance may exacerbate behavioral and biological quality of life (QoL), shoulder impairment, and daily activities.

Neuromuscular electrical stimulation (NMES) facilitates in blood circulation, muscle strength enhancement, tissue repair and analgesia by stimulating the selected muscles to induce muscle contraction following the depolarization of motor neurons (22, 23). It has discovered that stimulating the interscapular musculature, deltoid, triceps, and wrist extensors during a reaching task enhanced task performance by augmenting the ROM in active shoulder flexion and elbow extension (24). Researchers found that the cortical excitability was enhanced during motor activities subsequent to a brief administration of NMES combined with volitional activity in the upper extremity (25). Furthermore, a study involving 25 healthy participants revealed that NMES with voluntary movement of the stimulated muscles enhanced cortical excitability (26). The advantageous adaptation in the cerebral cortex may happen in neuroplasticity and functional modifications through NMES.

The maladaptive neuroplastic alterations are linked to FS, suggesting that treatment focused on reversing these changes is necessary (27). Repetitive transcranial magnetic stimulation (rTMS) is a non-invasive neuromodulation technique works by generating rapidly changing magnetic fields in specific regions of the cerebral cortex, which induce neuronal depolarization. This process can modulate neuronal excitability and synaptic plasticity in the underlying brain structures to restore cortical networks and may serve as suitable management alternatives for individuals with FS. The primary motor cortex (M1), located in the precentral gyrus of the frontal lobe is traditionally considered the brain region responsible for controlling voluntary movements of the contralateral limbs, however, recent studies have revealed that M1 also demonstrates neuroplasticity in relation to pain. The M1 neuronal projections to the periaqueductal gray (PAG) circuit encode information regarding sensory hypersensitivity associated with pain. M1 neurons can also project to tertiary neural circuits that include the mediodorsal thalamus and nucleus accumbent, recording the negative emotional dimensions of pain (28). The recent systematic review has also demonstrated that M1-rTMS can effectively reduce neuropathic pain (29), with M1 serving as the principal stimulation target for rTMS-induced analgesia. Multiple experimental studies have demonstrated that M1-rTMS possesses enhanced efficacy in reducing pain intensity, markedly diminishing the perceived severity of induced pain (30). The effects of rTMS at different frequencies on analgesia and cortical excitability differs: high-frequency (≥5 Hz) rTMS enhances cortical excitability, whereas low-frequency (≤1 Hz) rTMS diminishes cortical excitability. Both high and low frequencies may elicit analgesic effects (31). But the exact neural processes by which cortical plasticity contributes to FS remain unidentified.

If peripheral and cortical alterations are associated with FS, then rTMS and NMES training may be beneficial in treating this ailment for which effective treatment remains elusive. Therefore, the present protocol will be designed for a patient and assessor blinded, sham-controlled, randomized clinical trial, which will include 3 groups: Sham rTMS +NMES group (Group A), the LF-rTMS+NMES group (Group B) and the HF- rTMS+NMES group (Group C) and. The purposes of this protocol are as follows:

Aim 1: To evaluate the efficacy of NMES combined with rTMS over the contralateral M1 area in reducing pain intensity and improving functional ability in patients with FS. And to compare the efficacy of LF-rTMS+NMES and HF-rTMS+NMES in patients with FS.

Aim 2: To investigate the correlation between the clinical efficacy and neuro-biomechanism of cortical alternation in patients with FS after conducting systematic evaluations both before and after treatment.

Aim 3: Based on this study protocol and its anticipated outcomes, clinicians can develop innovative management strategies for pain and motor function in patients with FS, aiming to achieve effective therapeutic results.

## Methods and analysis

### Study design

This will be an assessor and patients blinded, sham-controlled, randomized controlled clinical trial (RCT) involving a 4-week intervention and 6-month follow-up. A total of 117 patients with FS will be recruited and randomly assigned to the sham rTMS +NMES group (Group A), LF-rTMS+NMES group (Group B) and HF-rTMS+NMES group (Group C) at a ratio of 1:1:1. Figure 1 depicts a concise flowchart of the entire study, and Table 1 provides the schedule of events. The study protocol (2025-7th-HIRB-042) was approved by the Ethics Committee of the Seventh People’s Hospital of Shanghai University of Traditional Chinese Medicine and registered in the Chinese Clinical Trial Registry (ChiCTR2500098406).

**Figure 1 fig1:**
[figure not shown]
A brief flowchart of the entire study. FS, Frozen shoulder; CRP, conventional rehabilitation program; NMES, neuromuscular electrical stimulation; LF-rTMS, low-frequency repetitive transcranial magnetic stimulation; HF-rTMS, high-frequency repetitive transcranial magnetic stimulation; SF-36, 36-item short-form health survey; sEMG, surface electromyography; MEP, motor evoked potential; MRI, magnetic resonance imaging.

**Table 1 tab1:** Schedule of enrolment, intervention and assessments.

Study period							
Timepoint	Screening	Baseline	Treatment		Follow- up		
	-1 month	0	2 weeks	4 weeks	1 month	3 months	6 months
Enrolment							
Eligibility screen	✓						
Informed consent	✓						
Demographic information	✓						
Descriptive information		✓					
Randomisation		✓					
Allocation		✓					
Interventions							
Group A		↔					
Group B		↔					
Group C		↔					
Assessments							
CMS		✓	✓	✓	✓	✓	✓
polysomnography		✓	✓	✓	✓	✓	✓
SF-36		✓	✓	✓	✓	✓	✓
sEMG		✓	✓	✓	✓	✓	✓
MEP		✓	✓	✓	✓	✓	✓
GMWM/FC/subcortical nuclei volumes cortical thickness (MRI)		✓		✓			✓
Acceptability assessments							
Referral rate				✓			✓
Retention rate				✓			✓
Drop-out rate				✓			✓
Safety assessments							
Adverse event occur rate				✓			✓
Summary the study	s						✓

“✓“means things will be done. CMS, Constant-Murley Score; SF-36, 36-Item Short Form Survey; sEMG, surface Electromyography; MEP, motor evoked potential; GM, grey matter density; WM, white matter; FC, functional connectivity; MRI, magnetic resonance imaging.

